### Timeline and assessments

2.7

The study duration for each participant is 6 weeks from start to finish and 8 weeks in total for participants from groups 1, 2, 5, and 6, with three main measurement points: baseline (T0), post-Phase 1 (T1 at 6 weeks), and post-Phase 2 (T2 at 8 weeks). Additionally, brief self-reports are collected throughout the intervention period to track immediate effects and adherence.

**Week 0: Baseline (T0).** Upon enrollment and after screening, participants complete an online baseline questionnaire battery before any intervention. This includes demographic information, the Multidimensional Mood State Questionnaire (MDBF) (14), the GAD-7 (13), the Perceived Stress Scale (PSS-14) (15), the Pittsburgh Sleep Quality Index (PSQI) (16), the WHO-5 Well-Being Index (17), and the Penn State Worry Questionnaire (PSWQ, German short form) (18). These instruments establish baseline levels of relaxation, anxiety severity, perceived stress, sleep quality, psychological well-being, and trait worry, respectively. A subset of participants in Berlin also undergoes baseline physiological recording (continuous electrocardiogram (ECG) and pulse). The intervention commences on the day following completion of the baseline assessment.

**Weeks 1–6: Intervention Phase 1.** Participants follow the assigned intervention every two days (∼3 times per week). Before each session, they are prompted to rate their current subjective relaxation level using a simple Visual Analogue Scale (VAS) (e.g., “How relaxed do you feel right now?” on a 0–100 scale). Immediately after each session, whether hypnosis with or without essential oil, they rate their relaxation again on the VAS. These pre-post VAS measures for every session provide a running check of acute changes in relaxation per session and allow analysis of trends. During this phase, Groups 1, 2, 5, 6 use their essential oil aroma sticks during the hypnosis sessions as instructed, while Group 3 uses no essential oil (hypnosis only) and Group 4 simply continues with minimal intervention. The study platform tracks adherence.

**Week 6: Post-Intervention Assessment (T1).** At the end of week 6, after the last Phase 1 session, all participants complete the T1 online survey. This repeats the same set of standardized questionnaires as at baseline (MDBF Calmness-Restlessness, GAD-7, PSS-14, PSQI, WHO-5, PSWQ) to quantify changes in relaxation and secondary outcomes from T0 to T1. In addition, participants are asked an open-ended question about their experience by asking for example, “Please describe how you experienced the intervention.” and “How did you integrate the intervention into your daily life?” This qualitative prompt allows them to reflect on any perceived benefits, challenges, or routine they developed over the six weeks. The responses, entered as free text, will later be analyzed to gain insights into engagement, acceptability, and subjective impact. This approach further allows for the identification of unforeseen themes that may emerge in connection with the intervention. Participants in the physiology subgroup come into the lab around this time for their second physiological measurement.

**Weeks 7–8: Conditioning Phase 2.** These two weeks focus on testing conditioned relaxation. Participants in Groups 1, 2, 5, 6 now use the aroma stick alone every two days, without using the hypnosis audio. Group 1 continues with bergamot essential oil inhalation; Group 2 with lavender oil, both maintaining the same CS as in conditioning (match). Group 5 switches to lavender oil only, after being conditioned with bergamot, and Group 6 switches to bergamot oil only, after conditioning with lavender. Group 3 and Group 4 will not be followed up in this phase. As in Phase 1, participants in the active arms (1, 2, 5, 6) will record a VAS relaxation rating before and after each aroma exposure to quantify any immediate relaxation effect from the scent. This data will show whether merely inhaling the familiar essential oil produces a significant calmness boost, and whether that holds true only for the matching scent or also occurs with a mismatched scent).

**Week 8: Final Assessment (T2).** At the end of week 8, all participants, including groups 3 and 4, complete a T2 survey which again includes the MDBF Calmness-Restlessness subscale and the secondary outcome questionnaires (GAD-7, PSS-14, PSQI, WHO-5, PSWQ). This final measurement captures any further changes after the Phase 2 period.

Additionally, long-term follow-ups are planned at approx. 6- and 12-month post-intervention. Participants will be contacted via email to fill out a brief online follow-up survey. These follow-ups will primarily include open-ended questions asking participants to reflect on any lasting changes or benefits they attribute to the intervention, such as “How has your well-being changed in the months since participating in the study?”, “How has handling of stress changed in the months since participating in the study?” or “Have you continued to use any techniques or experienced any long-term effects?”. The responses will be analyzed qualitatively to explore the sustainability of the intervention's impact. These follow-ups are exploratory and voluntary; data will be pseudonymized and used to gauge any extended outcomes beyond the controlled trial period.

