**Figure 1 F1:**
[figure not shown]
Study overview and timeline. After online screening (GAD-7/PHQ-9), eligible participants are randomized (1:1:1:1:1:1) to six arms. Phase 1 (Acquisition; 6 weeks) involves self-hypnosis every ∼2 days, with or without essential oil exposure depending on group; pre/post-session relaxation is recorded via VAS. Phase 2 (Evocation; 2 weeks) tests conditioned responding: participants in aroma arms complete essential-oil exposure without hypnosis every ∼2 days (CS match = same oil as in Phase 1; CS mismatch = switched oil), with VAS recorded pre/post exposure. Assessments are conducted at baseline (T0), post-phase 1 (T1), and post-phase 2 (T2); follow-up surveys occur at 6 and 12 months without further application. An optional Berlin/Brandenburg subcohort undergoes exploratory physiological assessment (HRV, PWV) at the time points indicated. CS, conditioned stimulus; GAD-7, generalized anxiety disorder-7; PHQ-9, patient health questionnaire-9; HRV, heart rate variability; PWV, pulse wave variability; VAS, visual analogue scale.

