### Study groups

2.6

Participants are randomly assigned to one of six groups (arms) in a 1:1:1:1:1:1 ratio. Four groups are primary comparison arms for the main efficacy analysis at 6 weeks, and two additional groups are included for secondary analyses of conditioned stimulus specificity in Phase 2.

**Group 1: Hypnosis** + **Essential Oil (Bergamot).** Participants receive the self-hypnosis audio and inhale bergamot essential oil during each session in Phase 1. In Phase 2, they continue with bergamot oil only (no audio) on the same schedule. This is a conditioned stimulus (CS)-match condition where the same essential oil is used for conditioning and testing.

**Group 2: Hypnosis** + **Essential Oil (Lavender).** Participants receive the hypnosis audio plus lavender essential oil inhalation during Phase 1 sessions. In Phase 2, they use lavender oil only without hypnosis. This is the CS-match for lavender.

**Group 3: Hypnosis Only (No Oil).** Participants receive guided hypnosis sessions in Phase 1 with no aromatherapy. This controls for the effects of hypnosis alone. They do not use any aroma in Phase 2 either and effectively have no active intervention in weeks 7–8.

**Group 4: Minimal Intervention Control.** Participants do neither hypnosis nor essential oil in Phase 1. Instead, they may receive a minimal activity just to match time/expectation. This arm serves as a baseline and expectancy control. They also do not receive any aroma in Phase 2.

**Group 5: Hypnosis** + **Oil (Bergamot) → Switch to Lavender.** These participants start identical to Group 1 (hypnosis + bergamot oil in Phase 1). However, in Phase 2 they experience a CS-mismatch by switching to lavender without hypnosis. This group helps test if a different scent can trigger relaxation or if the effect is lost when the conditioned stimulus changes. It serves as a control for Group 1 in the conditioning analysis.

**Group 6: Hypnosis** + **Oil (Lavender) → Switch to Bergamot.** These participants mirror Group 2 initially (hypnosis + lavender in Phase 1), then switch to bergamot oil only in Phase 2, creating a CS-mismatch. This serves as a control for Group 2 to assess stimulus specificity.

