All groups 1, 2, 5, and 6 receive the full combined intervention (hypnosis + essential oil) in Phase 1, ensuring that Groups 5 and 6 have the same conditioning opportunity as their counterparts before the switch. Groups 3 and 4 allow us to isolate the effects of hypnosis itself (Group 3) and to account for any changes over time not attributable to the interventions (Group 4). Randomization is implemented via the SoSci Survey platform's built-in algorithm once participants are deemed eligible, ensuring allocation concealment. Because of the nature of the interventions, participants will know if they are using an oil or not (blinding is not feasible on the user level), but they will not be informed of the study hypotheses regarding which combination is expected to be most effective. The trial is single blinded in that the data analysts/statisticians will remain blind to group labels until after the primary analyses are completed, to prevent bias in outcome analysis.

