**Exploratory Hypothesis 2.3 (Moderators of Effect).** We will explore whether certain baseline factors moderate the intervention's effectiveness. Demographic factors like age, gender, or socioeconomic status might influence outcomes. For instance, it's possible that participants with higher initial anxiety, though still subthreshold, benefit more or less from the intervention, or that younger vs. older participants have different adherence rates. These analyses are exploratory and will be used to generate hypotheses for which subgroups respond best to this approach.

**Exploratory Hypothesis 2.4 (Physiological Effects).** We hypothesize that the combination of hypnosis and aromatherapy yields measurable physiological relaxation, reflected in increased parasympathetic activity or reduced sympathetic activity compared to hypnosis alone. In the laboratory subgroup, it is hypothesized that Group 1/2 (combined) will demonstrate larger increases in HRV, particularly high-frequency HRV, which is indicative of parasympathetic tone, and/or a greater reduction in heart rate and PWV from T0 to T1 than Group 3 (hypnosis only). This would suggest an additive effect of the essential oil on the body's relaxation response, consistent with objective evidence that an essential oil can modulate autonomic activity. However, given sample size limitations, this will be an exploratory outcome.

**Exploratory Hypothesis 2.5 (VAS Trajectory and Learning Effects).** By examining the VAS relaxation ratings collected before and after each session, we hypothesize that participants receiving the combined intervention will not only have larger acute relaxation gains per session on average than those in comparison groups, but they may also exhibit learning effects over time. A learning effect would manifest as gradually higher pre-session relaxation levels as weeks progress the participant's baseline state before each session improves, indicating they carry over some relaxed state or become more skilled at self-relaxation. We expect such effects might be most pronounced in those who undergo conditioning (Groups 1 and 2), potentially showing an upward drift in pre-session VAS scores and/or a plateau indicating habituation to relaxation. We will explore and graph these trajectories for insight into how the relaxation response develops with practice.

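### A within-group rise in pre-session VAS is labelled a learning effect, which needs a no-hypnosis arm rated on the same calendar, and it is unclear whether Group 4 rates at all

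*Protocol article*

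**What the plan says.** **Rating schedule.** Timeline and assessments (2.7) opens Phase 1 with a general statement: "Participants follow the assigned intervention every two days (∼3 times per week". The pre-session prompt names no group: "Before each session, they are prompted to rate their current subjective relaxation level using a simple Visual Analogue Scale (VAS". The post-session rating describes sessions as hypnosis: "Immediately after each session, whether hypnosis with or without essential oil, they rate their relaxation again on the VAS". The Figure 1 legend attaches the VAS to self-hypnosis, "with or without essential oil exposure depending on group; pre/post-session relaxation is recorded via VAS". Procedure (2.5.1) describes a session as listening to the hypnosis audio.

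**Group 4.** Study groups (2.6) gives this arm neither hypnosis nor oil and adds: "Instead, they may receive a minimal activity just to match time/expectation". The Phase 1 timeline says only that "Group 4 simply continues with minimal intervention". The same Study groups section gives the arm its purpose, namely "to account for any changes over time not attributable to the interventions (Group 4").

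**Hypothesis and analysis.** H2.5 (Hypotheses, 2.10) expects the combined intervention to show "larger acute relaxation gains per session on average than those in comparison groups", without listing those groups. It describes learning as a gradual rise in pre-session relaxation over the weeks. Data analysis (2.13) plans mixed models for the gain per session by group. It also plans a test, group by group, of whether pre-session relaxation rises over the six weeks, and calls such a rise a learning effect.

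**The concern.** A rise in pre-session VAS within one arm has several possible causes: skill or carry-over from practice, the passage of time, a calendar effect, or a change in how people use the scale after rating themselves many times. A within-group trend test adds these together. Giving the sum the name of one component is an error of attribution that a larger sample does not cure.

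The trial has an arm meant to account for change over time. It can do so for the VAS only if it is rated on the same calendar, and the article does not make clear that it is. If ratings are not collected from Group 4 in weeks 1 to 6, no later analysis can recover them. What H2.5 can conclude about learning from hypnosis practice depends on this.

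**Working it through.** No figure in the plan depends on this point, so there is none to reproduce. The check has three parts.

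**1. Does Group 4 rate?** The statements in 2.5.1, 2.6, 2.7, 2.13 and the Figure 1 legend divide as follows.

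| Points towards no VAS in Group 4 | Points towards VAS in Group 4 |
|---|---|
| A session is listening to the hypnosis audio (2.5.1) | All participants follow their assigned intervention every two days (2.7) |
| The post-session rating is worded for hypnosis with or without oil (2.7) | The pre-session prompt names no group (2.7) |
| The Figure 1 legend ties the VAS to self-hypnosis | The trend is to be tested for each group (2.13) |
| Group 4's activity is optional and not described (2.6) | Phase 2 names the arms that rate (1, 2, 5, 6); Phase 1 has no such restriction (2.7) |

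The text does not settle the question.

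**2. What each comparison identifies.** Write an arm's mean pre-session slope as a sum (an additive simplification): τ for time and repeated rating, π for hypnosis practice, ω for the added oil.

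- Groups 1, 2, 5 and 6: τ + π + ω
- Group 3: τ + π
- Group 4, if rated on the same calendar: τ

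Hence:

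- within-group trend in a combined arm: τ + π + ω, so a positive value does not show π > 0
- combined minus Group 3: ω only
- Group 3 minus Group 4: π
- combined minus Group 4: π + ω

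Group 3 therefore removes drift when the question is about the oil. Only Group 4 removes it when the question is about learning from practice.

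**3. How easily drift alone passes the within-group test.** Let D be the mean non-specific drift divided by the between-person SD of drift, with no learning (π = ω = 0). D is an assumption, because the article gives no value. For a two-sided 5% test with n participants:

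P(reject) = Φ(D√n − 1.96) + Φ(−D√n − 1.96)

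The inputs are n = 105, the planned arm size, and n = 68, which is what remains of 105 at the roughly 35% dropout the sample size section allows for (105 × 0.65 = 68.25).

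Example: D = 0.2 and n = 105 give D√n = 0.2 × 10.247 = 2.049, and Φ(0.089) + Φ(−4.009) = 0.54.

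| D | n = 105 | n = 68 |
|---|---|---|
| 0.1 | 0.18 | 0.13 |
| 0.2 | 0.54 | 0.38 |
| 0.3 | 0.87 | 0.70 |

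The test is working correctly here: it detects a trend that exists. The error lies in calling that trend learning. A slope difference between two arms with the same drift keeps its nominal 5% error rate whatever D is.

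Each participant who rates at every session gives many ratings. Every two days for 42 days is 42 / 2 = 21 sessions and 42 ratings; three times a week is 6 × 3 = 18 sessions and 36 ratings. Repeated rating is therefore a realistic source of drift, although the article gives no information on its size.

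**The case against.** **Group 4 may well rate.** The general opening of the Phase 1 schedule, the ungrouped pre-session prompt and the per-group trend analysis all fit that reading, and the authors name the rating arms when they restrict the VAS in Phase 2. This stands. A reader might infer from the hypnosis wording that Group 4 certainly gives no ratings, but the article never says so. If Group 4 does rate, the definition of learning by a within-group trend is still wrong, and the activity around which it rates is still undescribed.

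**Operational detail belongs in the full protocol.** This is fair for the content of the minimal activity and the prompt settings. It does not cover the learning-effect definition, which the article itself states.

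**Group 3 already controls for time and rating.** This is correct for H2.5's comparative claims about the combined arms, since Group 3 follows the same session schedule and gives the same ratings. It is not correct for learning from hypnosis practice, which Group 3 shares.

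**H2.5 is exploratory.** This is true: no sample size or error rate rests on it, and the authors mean to explore and graph the trajectories. It limits the weight of the point. It does not make a within-group trend interpretable as learning.

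**Conclusion.** The concern holds in a limited form. The Data analysis section equates a within-group upward trend in pre-session VAS with learning, and that inference fails without a no-hypnosis arm rated on the same calendar. Whether Group 4 provides this is unclear: the VAS wording suggests not, and the per-group analysis suggests that it does. Under an assumed drift of 0.1 to 0.3 SD, the within-group test would flag a trend in 18% to 87% of trials at 105 per arm (13% to 70% at 68) with no learning present. These figures illustrate the mechanism and do not estimate the actual drift.

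A reader might go further and infer that the week-6 comparison with Group 4 on MDBF calmness is biased because the hypnosis arms monitor their relaxation far more often. The documents do not support that. It presumes that Group 4 gives no ratings, which is not stated, and nothing in the article gives a size for any rating effect. The contrasts of Groups 1 and 2 with Group 3 would be untouched in any case. The point concerns what H2.5 can conclude, and the primary analysis is not shown to be affected.

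**What to change.** 1. **Redefine the learning effect** in Data analysis as a group-by-session difference in pre-session VAS slope against Group 4. Report within-group trends descriptively, without the learning label.
2. **State that Group 4 rates.** Have the survey platform prompt this arm for VAS ratings on the same every-two-days calendar, before and after its minimal activity. Say what that activity is, so that its pre-post change has a meaning.
3. **Name the comparison groups in H2.5**, separately for the gain per session and for the slope.
4. **If Group 4 does not rate**, say so. Limit H2.5 to slope and gain differences between the combined arms (1, 2, 5, 6) and Group 3, state that these isolate only the added effect of the oil, and do not describe any within-group trend as learning.

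Items 1, 3 and 4 cost a few sentences. Item 2 costs a prompt schedule on a platform already in use and some added burden for Group 4. That arm would then be a rating-matched control, which should be stated when its results are interpreted.

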After six weeks of regular practice, Phase 1 concludes with the T1 assessment. Immediately thereafter, Phase 2 (weeks 7–8) begins, lasting two additional weeks. In Phase 2, participants no longer do the hypnosis sessions; instead, they engage in essential oil exposure alone every two days, continuing with the same schedule of thrice weekly exposure. During these sessions, they will inhale from the aroma stick, containing an essential oil, for a brief period (several minutes) but without any accompanying audio or hypnosis. The purpose is to test whether the essential oil itself can elicit a relaxation response after the conditioning in Phase 1. Some groups will receive the same oil in Phase 2 as they did during Phase 1 (matched condition), while others will receive a different oil (mismatched condition) to test the stimulus specificity of the conditioned response. No explicit relaxation exercise is given in this phase aside from the essential oil exposure. Participants still rate their mood before and after each essential oil exposure, as described below, to gauge any relaxation effect purely from the scent.

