
However, given the small subgroup sample, these physiological analyses are exploratory. The measurements are carefully scheduled to avoid acute effects of a session (participants do not do a hypnosis session right before the measurement; it's a resting baseline capture). The present sub-study offers an objective evaluation of the intervention's impact on bodily stress arousal, in addition to its subjective effects.

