### Outcomes

2.9

The primary outcome of the trial is subjective relaxation, operationalized as the score on the “Calmness-Restlessness” subscale of the Multidimensional Mood State Questionnaire (MDBF) (14). This subscale directly assesses the participant's current state of inner calm vs. agitation, making it a suitable primary endpoint for an intervention aiming to increase relaxation. The MDMQ has demonstrated good internal consistency in prior research, with Cronbach's *α* between 0.86 and 0.94., depending on the population and setting (14). Primary analysis focuses on the change in this relaxation score from baseline (T0) to post-intervention (T1, week 6). The key comparison is between the combined Hypnosis + Essential Oil groups (1 and 2) and the control conditions (Hypnosis-only and Minimal Intervention). Several secondary outcomes will also be examined (all measured at T0, T1, and T2 using validated self-report instruments).

**Anxiety symptoms.** GAD-7 (13), a brief scale measuring the frequency of core GAD symptoms (worry, tension, etc.) in the past two weeks. It will indicate if the intervention reduces overall anxiety levels.

**Perceived stress.** PSS-14 (15) gauges the extent to which situations in life are appraised as stressful. We will see if participants report feeling less overwhelmed by stress after the intervention.

**Sleep quality.** PSQI (16) assesses sleep patterns and disturbances over the past month. Given the calming nature of the intervention, improvements in sleep quality (lower PSQI scores) are expected in the active groups, as anxiety and sleep are often linked.

**Well-being.** WHO-5 Well-Being Index (17), a short measure of positive mood and vitality. This captures any boost in general mental well-being or mood that might accompany stress reduction.

**Worry tendency.** PSWQ (20), German short form (PSWQ-d) measures trait worry severity. We will explore whether regular relaxation practice and perhaps improved coping reduce habitual worry levels in participants.

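### T1 follows the last Phase 1 session with no minimum gap specified, so the primary contrast in a momentary score cannot separate an acute session effect from six weeks of practice

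*Protocol article*

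**What the plan says.** Section 2.9 (Outcomes) describes the MDBF calmness subscale as a measure of the participant's "current state of inner calm vs. agitation". The primary analysis is the change in this score from T0 to T1.

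Section 2.7 (Timeline and assessments) fixes the two time points. At T0, "participants complete an online baseline questionnaire battery before any intervention", and "The intervention commences on the day following completion of the baseline assessment". At T1, "At the end of week 6, after the last Phase 1 session, all participants complete the T1 online survey". Section 2.5.1 (Procedure) adds that "Phase 1 concludes with the T1 assessment" and that Phase 2 starts straight after it. No minimum interval between the last session and T1 is given.

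Section 2.7 also has participants rate relaxation on a VAS before and after every session, to follow acute changes. For the laboratory recordings of HRV and PWV, section 2.8 (Physiological subgroup) states: "The measurements are carefully scheduled to avoid acute effects of a session". Section 2.6 (Study groups) gives Group 4 neither hypnosis nor oil in Phase 1. The primary hypothesis in section 2.10 concerns greater improvement in relaxation once the six-week intervention has been completed.

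**The concern.** A momentary score depends on what the person did just before answering. At T0 nobody has had a session. At T1, participants in Groups 1 and 2 may have just finished hypnosis with scent and those in Group 3 hypnosis alone, while Group 4 has had neither. The audio and the survey are both delivered online, and nothing in the article stops a participant from answering T1 minutes after the recording ends.

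A higher T1 score in the hypnosis arms could then reflect one recent session, six weeks of practice, or both. The first would be a much weaker basis for the preventive use that the Discussion has in view. The protocol guards against acute effects in an exploratory substudy and measures them separately by VAS, but states no such safeguard for the primary endpoint.

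**Working it through.** The article gives no figure for the acute effect, so there is nothing to reproduce. The check has three steps.

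**1. The measurement conditions side by side**

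| Measurement | Position relative to sessions |
|---|---|
| MDBF at T0 | before any session; sessions start the next day |
| MDBF at T1, Groups 1 and 2 | after hypnosis with scent, gap not specified |
| MDBF at T1, Group 3 | after hypnosis, gap not specified |
| MDBF at T1, Group 4 | no hypnosis or oil session |
| HRV/PWV at T1 | scheduled away from sessions |
| VAS | before and after each session |

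Sessions are two days apart, so the gap before T1 could be anything from minutes to about two days.

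**2. Where an acute effect enters each contrast**

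Let *a* be the acute calmness gain from a hypnosis session and *s* any additional acute gain from scent, both in SD units. Let *p* be the share of hypnosis-arm participants who answer T1 while the gain is still present. Assume that *p* is equal across Groups 1 to 3 and that Group 4's minimal activity has no acute effect. The acute part of each contrast is then:

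- Group 1 or 2 vs Group 4: *p*(*a* + *s*)
- Groups 1 and 2 vs Groups 3 and 4, equal weights: *p*(*a* + *s*) − *pa*/2 = *p*(*a*/2 + *s*)
- Group 1 or 2 vs Group 3: *p*(*a* + *s*) − *pa* = *ps*

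With *s* = 0 and assumed values of *a* and *p*:

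| *a* | *p* | vs Group 4 | 1 and 2 vs 3 and 4 | vs Group 3 |
|---|---|---|---|---|
| 0.3 | 0.25 | 0.3 × 0.25 = 0.075 | 0.0375 | 0 |
| 0.5 | 0.50 | 0.5 × 0.50 = 0.25 | 0.125 | 0 |
| 0.8 | 0.75 | 0.8 × 0.75 = 0.60 | 0.30 | 0 |

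Section 2.11 gives d of about 0.35 to 0.40 as the pairwise equivalent of its planned effect. The middle row against Group 4 is 0.25/0.35 = 71% of the lower value. For Groups 1 and 2 against 3 and 4, 0.125/0.35 = 36%.

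**3. Could an acute effect alone give a significant result?**

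Take a lasting effect of zero, 105 analysed per arm, two-sided α = 0.05 without multiplicity correction, and 20% of variance explained by baseline (section 2.11). The standard error of a pairwise difference is √0.8 × √(2/105) = 0.894 × 0.138 = 0.123. For an acute between-arm difference *d*, the probability of significance is about Φ(*pd*/0.123 − 1.96). For *d* = 0.35 and *p* = 0.5 this is Φ(1.42 − 1.96) = 0.29. Against Group 4, read *d* as *a* + *s*; against Group 3, as *s* alone.

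| *d* | *p* = 25% | 50% | 75% | 100% |
|---|---|---|---|---|
| 0.20 | 0.06 | 0.13 | 0.23 | 0.37 |
| 0.35 | 0.11 | 0.29 | 0.57 | 0.81 |
| 0.50 | 0.17 | 0.53 | 0.86 | 0.98 |

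So a significant pairwise result with no lasting effect is possible, and likely only if many participants answer soon after a session.

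**The case against.** The strongest reply is that section 2.7 states an order and not an interval. It uses the word immediately for the post-session VAS but not for T1. The document is a journal article, and the rule that opens the survey may stand in the full protocol. A reader might infer that T1 is placed directly after a session; the text does not say so. This limits the claim to a gap left unspecified. It does not remove the point, because the article does fix T1 relative to the last session and does state a separation rule for the physiology alone.

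A reader might also call the primary contrast biased. That goes too far. An acute gain from an assigned session is a causal effect of that assignment, so randomisation still protects the comparison; only its interpretation is open. Nor does the hypothesis use the word sustained, and the Introduction mentions acute efficacy as an aim. That is fair, but the hypothesis refers to the completed six-week programme, and the article never says that an acute effect is meant to count.

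The design offers partial help. The trend in pre-session VAS could separate carry-over from acute gain, and the GAD-7 and PSQI cover longer recall periods. But the VAS trend is exploratory, and none of these is the primary outcome.

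Finally, extending the point to T2 has no basis in the text, which places T2 only at the end of week 8. Section 2.5.1 already puts Phase 2 after T1.

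**Conclusion.** The point holds as one of interpretation. As described, the T0 to T1 contrast in a momentary score cannot tell an acute post-session effect from the effect of six weeks of practice.

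The exposure differs by contrast. It is largest against Group 4 and about half as large for Groups 1 and 2 against 3 and 4. For 1 vs 3 and 2 vs 3, which section 2.13 singles out, it is limited to any acute scent effect. It is tempting to say that most of the planned effect could be acute. The 71% behind that statement applies only against Group 4 and rests on an assumed gain of 0.5 SD in half of the participants, neither of which comes from the documents. The cancellation against Group 3 in turn assumes similar timing of T1 in the hypnosis arms. The matter does not invalidate the trial, but it should be settled because the remedy is cheap and later analysis cannot fully repair it, least of all if the time since the last session is not kept.

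**What to change.** Open the T1 survey in SoSci on a session-free day, for example the day after the last Phase 1 session and before the first Phase 2 exposure, with the same calendar rule for all arms including Group 4. The session schedule need not change. On a strict two-day rhythm from day 1, the 21st session falls on day 1 + 2 × 20 = 41, which leaves day 42 free and still within week 6.

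Store the time between the last session and T1 submission. Add a sensitivity analysis that excludes T1 surveys completed on a session day.

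If the acute effect is meant to count, say so in sections 2.9 and 2.10 as part of the estimand, and word the conclusions to match.

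The cost is one scheduling rule and a sentence or two in the protocol. T1 moves by about one day, and completion may dip slightly because the survey no longer follows directly on a session.
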